### Data collection

#### Demographics

Information regarding age, gender, ethnicity, home and work postcodes will be collected at baseline. The English Index of Multiple Deprivation (IMD; Department for Communities and Local Government, 2015) [70] based on full home postcode will be determined as a measure of community socioeconomic status (SES). Cancer stage at diagnosis and treatment pathway information will be obtained from the clinical team.

#### Feasibility and acceptability

To assess feasibility of recruitment, the number of individuals that attend the clinics and the number that are deemed eligible will be recorded. Recruitment rates, consent rates and willingness to be randomised will be recorded. Retention rates will be determined based on the number of individuals that complete the intervention, post testing, and follow-up measures. Adherence rates to study procedures will be recorded.

The acceptability of the recruitment methods and individuals’ receptiveness to the study will be explored through semi-structured one-to-one interviews with the clinical care team. The acceptability of the study procedures, including data collection methods, and the intervention will be explored through semi-structured one-to-one interviews of all study participants and instructors. These interviews will be conducted by a member of the research team. Interview questions for instructors will focus on factors that impact intervention delivery, including intervention content, facilities, time and burden. Interview questions for participants will focus on thoughts and feelings regarding participation in the intervention and data collection processes. The research team will track the costs and resources required for running the trial. Life Cycle will track the staff costing of intervention delivery and from the maintenance service. This information will be shared with the University of Bristol research team.

#### Intervention fidelity

The degree to which the intervention was delivered and received as intended (implementation) will be evaluated following criteria proposed by Lambert and colleagues [71]. Specifically, all instructors delivering the intervention will undertake training which will include information on the benefits of PA for individuals with cancer and training on how to engage in discussions around personal health. A separate training session focused on the theoretical bases of the intervention, the principles of motivational interviewing and the specific intervention content will also be delivered. Training will include role plays with supervised feedback which will be documented. Following the training, instructor’s intervention delivery will be observed by a member of the research team and observation checklists completed to record instructors’ delivery of the intervention content, receipt of the intervention by participants and enactment of the behavioural skills. Throughout the intervention, instructors will be asked to complete checklists to ascertain what skills training and discussions occurred during each session.

Intervention intensity, recorded by instructors, will be determined through recording of the number of intervention sessions attended by participants as well as the volume of email and telephone contact between instructors and participants. At the end of the study, information on attendance to intervention sessions and tasks completed within each session will be passed from Life Cycle to the research team. Participant’s ID, and not names, will be recorded on intervention documentation.

#### Process evaluation

To explore the mechanisms of impact, semi-structured interviews will be conducted with participants in the intervention group to identify barriers and enablers to engaging in e-cycling. The interviews will be guided by the Theoretical Domains Framework (TDF) to descriptively link the identified barriers and facilitators to pathways of behaviour change. The TDF is an integrative framework that synthesises 33 psychological theories and 128 constructs to understand the broad influences on behaviour. The TDF is an elaboration of the COM-B model, an evidence-based model identifying three key sources that interact to influence behaviour, namely capability, opportunity and motivation [65]. These interviews will help to identify how the intervention impacts behaviour and to determine contextual factors that influence the intervention.

#### Assessment of harm

Participants will be asked to report adverse events resulting from e-cycling (e.g. musculoskeletal problems, falls or road traffic incidents) by calling the study phone line. All adverse events will be immediately documented in the study master file and if required reported to the study sponsor and appropriate NHS trust as per standard procedures. Each month, the number and types of adverse events that have taken place will be shared with the Trial Steering Committee to determine whether it is appropriate for the trial to continue. Adverse events that mean the participant is unable to continue with the intervention will also be documented under retention rates. Qualitative interviews will be used to explore any unintended consequences that arise from participation in the study.

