### Study aims and objectives

The *primary* aim of this study is to test the feasibility of conducting two pilot randomised controlled e-cycling interventions among individuals with PCa (*CRANK-P*) and BC (*CRANK-B*). Two pilot RCTs will be conducted because these different clinical populations have different recruitment and treatment pathways. However, the primary aim of the two trials is the same and will be addressed by answering the following questions:Can individuals with PCa/BC be recruited to an e-cycling trial?Are participants’ willing to be randomised, do they remain in the study and adhere to the intervention and data collection methods, and what are the rates of harmful events?Can the intervention be implemented as intended?Are the intervention and study procedures acceptable to participants, instructors and the clinical team?What are participants’ experiences of e-cycling?

While the pilot RCTs will be insufficiently powered to statistically examine the effectiveness of the intervention on outcomes, they provide an opportunity to investigate the potential promise of the intervention. As such, the *secondary* aim is to examine the association between the intervention and outcome measures to determine intervention promise. To address this aim, the following question will be answered:6.What is the potential effect of the intervention on a range of individual health and behavioural outcomes?

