#### Control group

Individuals assigned to the waitlist control after baseline data collection (T0) will receive two phone calls from the researcher at approximately weeks 4 and 8 to maintain engagement in the study. During these phone calls, the researcher will ask participants about how their cancer treatment is going and will direct participants to cancer support groups in line with standard care procedures. Between post-intervention data collection (T1) and 3-month follow-up data collection (T2), individuals will not be contacted. After the 3-month follow-up, individuals in the control condition will be offered training session 1 and loaned an e-bike for 3 months. Sessions 2, 3 and 4 will not be conducted. Participants will be asked to report any contact they have with other individuals in the study to ensure no contamination between conditions has occurred.

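### Adverse events are solicited only if the participant blames e-cycling and phones in, so harm counts are probably incomplete and not comparable between arms

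*Protocol article*

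**What the plan says.** Question 2 of the primary aim (Study aims and objectives) includes "what are the rates of harmful events". Table 3 lists the number of harmful events as an outcome, taken from study records and summarised as frequencies and percentages.

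The section Assessment of harm describes collection. "Participants will be asked to report adverse events resulting from e-cycling", and they do so "by calling the study phone line". It then states: "All adverse events will be immediately documented in the study master file". Oversight follows: "Each month, the number and types of adverse events that have taken place will be shared with the Trial Steering Committee", the purpose being "to determine whether it is appropriate for the trial to continue". A qualitative route is added: "Qualitative interviews will be used to explore any unintended consequences that arise from participation in the study".

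Under Control group, controls "will receive two phone calls from the researcher at approximately weeks 4 and 8". The described content is how cancer treatment is going and signposting to support groups. They are not contacted between T1 and T2, and they are offered a trial e-bike only after T2.

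**The concern.** An event reaches the file by the solicited route only if it passes two filters: the participant must think e-cycling caused it, and must then take the initiative to call. For controls before T2 the first filter removes nearly everything, because they have no trial e-bike. A control count near zero would then be produced by the way the question is put and would not be an observation.

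This matters for three reasons. Harm rates are part of the primary aim. The Trial Steering Committee reviews counts monthly with continuation in view. And CRANK-P enrols men with high-risk localised, node-positive or metastatic disease, in whom background events are plausible. Falls, symptoms or admissions that nobody links to the bike are not solicited in either arm, nor are delayed effects of study procedures such as the maximal exercise test or venepuncture. Events not collected prospectively cannot be reliably recovered at the analysis stage.

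**Working it through.** The article states no harm rate and no sample size based on harms, so there is no figure to reproduce. The 40 per trial rests on recommendations for estimating a standard deviation and on e-bike supply (Sample size).

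**Step 1: the text side by side.**

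| Element | What is described |
|---|---|
| Needed | Rates of harmful events (primary aim, question 2; Table 3) |
| Solicited | Events the participant attributes to e-cycling, by a call the participant starts |
| Documented | All adverse events, with no route named for the others |
| Controls to T1 | Two researcher calls, no adverse event question described |
| Controls T1 to T2 | No contact |
| Controls' trial e-bike | After T2 only |

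The solicited scope is narrower than both the documented scope and the question to be answered.

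**Step 2: no true effect, but attribution possible in one arm only.** Input from the article: n = 20 per arm in each trial. Assumptions: the background rate p of musculoskeletal problems or falls is equal in both arms, 10% to 50%; a share a of 25% to 100% is attributed to e-cycling and phoned in; controls phone in none.

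- Recorded in the intervention arm = n × p × a. Lowest: 20 × 0.10 × 0.25 = 0.5. Highest: 20 × 0.50 × 1.00 = 10.
- Recorded in controls: about 0.
- Apparent difference = p × a, from 0.10 × 0.25 = 2.5 to 0.50 × 1.00 = 50 percentage points, when the true difference is 0.

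**Step 3: real e-cycling events, incompletely reported.** Assumptions: true probability q per participant 10% to 30%; share phoned in r 30% to 80%.

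- Expected recorded = n × q × r, from 20 × 0.10 × 0.30 = 0.6 to 20 × 0.30 × 0.80 = 4.8.
- P(none recorded) = (1 − q × r)^20, from (1 − 0.03)^20 = 54% to (1 − 0.24)^20 = 0.4%.

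Steps 2 and 3 push in opposite directions: the first creates a false excess, the second hides real harm.

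**Step 4: what sample size alone does.** With complete capture, 0 of 20 gives an upper 95% bound of 1 − 0.05^(1/20) = 13.9% one-sided, or 1 − 0.025^(1/20) = 16.8% two-sided exact; 2 of 20 gives an exact two-sided interval of 1.2% to 31.7%. These limits come from n = 20. They do not measure the ascertainment problem, and better collection would not narrow them.

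**The case against.** Several stronger readings are tempting, and the article does not support them.

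- **That the control arm yields no harms data.** The documentation sentence and the reports to the Trial Steering Committee are not limited to e-cycling or to one arm. Feasibility and acceptability plans interviews with all study participants, and interviews are to explore unintended consequences. The control calls ask about cancer treatment, and questionnaires measure symptoms in both arms. Some control information will arise. It is unsystematic or indirect, and qualitative interviews do not supply a rate or a monthly count.
- **That events in the exercise tests are missed.** Two researchers attend, with ECG, oxygen saturation and blood pressure monitored throughout (Cardiopulmonary exercise testing). They would see an event during the test. Only delayed effects are at risk.
- **That the harm figures cannot be interpreted at all.** The pilot is descriptive and question 2 does not ask for a between-arm difference. A count of self-attributed events among people given e-bikes can be read, as probably incomplete.
- **That e-cycling will look safer than it is.** That is one direction only; a near-empty control count pushes any contrast the other way.

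It is also fair to say that a journal article condenses, and that adverse event forms and relatedness assessment commonly sit in the full protocol. Their absence is not the point here. The restriction to events resulting from e-cycling is printed, and it does not match the sentence that follows it. That part of the concern stands.

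**Conclusion.** The concern holds in a limited form. Followed as written, the plan gives a probably incomplete, self-attributed count in the intervention arm and no systematic capture in controls. That count supports neither a comparison between arms nor an estimate of excess over background, and the monthly continuation review would rest on counts whose only solicited source is filtered in this way. Quantitative analysis promises descriptive comparisons between arms in a sentence that follows the one on adverse events; if it is meant to cover them, the comparison would not be valid.

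The size cannot be fixed from the article. Under the stated assumptions, a false excess of 2.5 to 50 percentage points and a 0.4% to 54% chance of recording no event despite real harm are both possible. The attribution and reporting shares and the event rates are assumed, not taken from the article. Should-fix is the right grade for a descriptive pilot without hypothesis tests.

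**What to change.** Reword Assessment of harm so that all adverse events are solicited whatever their cause, including those after study procedures, which also reconciles the solicited scope with the documented scope. Then:

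1. The research team asks the same short open question in both arms at T1 and T2, and at about weeks 4 and 8.
2. At weeks 4 and 8, use the same form and the same type of asker in each arm. The existing contacts do not suffice as they are: they are instructor sessions in one arm and researcher calls in the other, and a different asker or setting could itself create a between-arm difference.
3. Keep the phone line for immediate reports.
4. Record every event first; the research team assigns relatedness afterwards.
5. Tabulate events by arm for the Trial Steering Committee and the final report.

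Cost: one short form, a brief additional researcher contact with intervention participants at weeks 4 and 8, and more unrelated events to record. The change does not alter the sample size or the intervention, and it does not improve precision beyond what 20 per arm allows.

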#### Outcome measures

Unless stated otherwise, outcome measures will be assessed at baseline (T0), immediately post-intervention (T1) and at 3-month follow-up (T2) and will be collected in both trials.

##### Anthropometrics

Participants will be asked to take off shoes and remove heavy clothing. Body weight will be assessed to the nearest 0.1 kg using digital scales (TANITA Corp, Tokyo, Japan), and height will be assessed to the nearest 0.1 cm (SECA, 700 SECA Hamburg, Germany). These measures will be used to calculate BMI (kg/m^2^). Waist circumference will be measured using a non-stretch tape measure to the nearest 0.1 cm, based on World Health Organization guidelines [72]. Waist circumference measurements will be taken twice, and the average of those measures calculated.

##### Biochemical variables

Blood samples will be obtained by venepuncture of the antecubital fossa from individuals in a fasted state (≥ 8-h overnight fast) to measure glucose, insulin, insulin-like growth factor (IGF) I and II, IGF-binding protein 2 and IGF-binding protein 3. In CRANK-P, prostate-specific antigen (PSA) will also be measured. A total of 8 mL of blood will be taken at this time.

All blood samples will be transported, using a sealed container, immediately to the biochemistry laboratory at the Bristol Royal Infirmary where they will be centrifuged and the serum aliquoted prior to freezing at − 80 °C. Samples will be batch analysed at the end of the study. Glucose, insulin and lipids will be analysed using a Roche Cobas C701 analyser (Roche Diagnostics, Rotkreuz, Switzerland). IGF-I, IGF-II and IGFBP-3 will be analysed using radioimmunoassay, and IGFBP-2 will be analysed using enzyme-linked immunosorbent assay (ELISA). PSA will be analysed using a Roche Cobas C602 analyser. Insulin, glucose, lipids and PSA will be analysed at the USTAR laboratory. IGF factor samples will be transported to the Metabolic Endocrinology Group at the Learning and Research Building, Southmead, North Bristol, where they will be analysed. Basal insulin and glucose values will be used to calculate insulin resistance and beta-cell function using the homeostasis model assessment calculator (University of Oxford, Diabetes, Trial Unit).

##### Generic health-related quality of life (HRQoL)

The EuroQol-5 dimension-5 level survey (EQ-5D-5L) will be used to measure generic quality of life. The measure classifies health into five dimensions (mobility, self-care, usual activities, pain/discomfort, anxiety/depression) with five response categories including no problems, slight problems, moderate problems, severe problems and unable to/extreme problems [73]. Responses are coded as single-digit numbers which express the severity level selected in each dimension in a descriptive manner to generate a health state profile. From this, a health state index score will be calculated from individual health profiles using the England-specific value set [74]. The 5Q-5D-5L also includes a vertical visual analogue scale for respondents to self-assess their overall health based on ‘how good or bad your health is today’ with responses ranging from 0 to 100, where 100 represents ‘the best health you can imagine’. This measure has been widely used to assess generic health-related quality of life in cancer populations in response to exercise interventions [75–77] and is the most widely used measure of HRQoL internationally [78].

##### Cancer-specific health-related quality of life

The European Organisation for Research and Treatment of Cancer Core Quality-of-Life Questionnaire (EORTC QLQ-C30) will be collected to assess cancer-specific HRQoL. In addition, in CRANK-P, the 25-item PCa-specific (EORTC PR-25) questionnaire module will be collected, while in CRANK-B, the 45-item BC-specific (EORTC BR-45) questionnaire module will be collected. The EORTC QLQ-C30 is a 30-item questionnaire developed to assess general cancer-related aspects of quality of life covering the most common cancer symptoms (pain, fatigue, nausea, vomiting) and functional outcomes including physical, role, social, emotional and cognitive functioning. Items are scored on a 4-point Likert scale ranging from 1 (not at all) to 4 (very much), and a raw score is calculated for each multi-item scale. Raw scores are linearly transformed to a 0 to 100 scale for global health, functionality and symptoms [79]. The EORTC QLQ-C30 is an internationally validated measure and is the most widely used questionnaire for the assessment of HRQoL in cancer clinical trials [80–82]. Higher functional scores represent better functioning, a high score for global health status represents a higher quality of life and higher symptom scores indicate more severe symptoms.

The EORTC PR-25 is a 25-item PCa-specific questionnaire module designed to supplement the EORTC QLQ C-30 [83] and will be used in the current study to gather more PCa-specific HRQoL information. The PR-25 is composed of one single-item measure and five multi-item subscales to provide four symptom scores (urinary symptoms [eight items], bowel symptoms [four items], hormonal treatment-related symptoms [six items], incontinence aid [one item]) and two functional scores (sexual activity [two items] and sexual functioning [four items]). PR-25 sexual function items are completed only by those respondents who have been sexually active over the preceding 4 weeks. Items are scored on a 4-point Likert scale ranging from 1 (not at all) to 4 (very much), and a raw score is calculated for each multi-item scale. Raw scores are linearly transformed to a 0 to 100 scale. Higher functional scores represent better functioning, and higher symptom scores indicate more severe symptoms.

The EORTC BR-45 is a 45-item BC-specific questionnaire module designed to supplement the EORTC QLQ C-30 and will be used in the current study to gather more BC-specific HRQoL information. The BR-45 is composed of five function scores (body image [four items], future perspective [one item], sexual functioning [two items], sexual enjoyment [one item], breast satisfaction [two items]) and seven symptom scores (systemic therapy side-effects [seven items], upset by hair loss [one item], arm symptoms [three items], breast symptoms [four items], endocrine therapy symptoms [ten items], skin/mucosa symptoms [six items], endocrine sexual symptoms [four items]). Items are scored on a 4-point Likert scale ranging from 1 (not at all) to 4 (very much), and a raw score is calculated for each multi-item scale. Raw scores are linearly transformed for functional scales and symptom scales ranging from 0 to 100. As with PR-25, higher scores reflect more symptoms or higher levels of functioning. The BC-specific module of the EORTC is considered the standard instrument for measuring QoL in patients with both early and metastatic BC [84, 85].

##### Urinary health (CRANK-P)

The International Consultation on Incontinence Questionnaire Male Lower Urinary Tract Symptoms Module (ICIQ-MLUTS) will be used to evaluate male lower urinary tract symptoms [86, 87]. This measure assesses the prevalence and bother of 13 urinary symptoms as they were experienced on average over the past 4 weeks. Prevalence is scored on a scale from 0 (never) to 4 (all of the time), while bother of each of the 13 symptoms is scored on a scale of 0 (not at all) to 10 (a great deal). The questionnaire contains two predefined domains (adding up the scores of individual items): a void domain (maximum score 20 for prevalence and 50 for bother) and an incontinence domain (maximum score 24 for prevalence and 60 for bother). This measure has been found to be a valid and reliable instrument for evaluating lower urinary tract symptoms in men [87].

##### Erectile dysfunction (CRANK-P)

The International Index of Erectile Function (IIEF) will be used to measure erectile dysfunction. This 15-item measure is designed to diagnose the presence and severity of erectile dysfunction. Each item is scored from 1 to 5 or 0 to 5, and summary scores are created for the 4 domains of male sexual function: erectile function (maximum score 30), orgasmic function (maximum score 10), sexual desire (maximum score 10) and intercourse satisfaction (maximum score 15) and two questions relating to overall satisfaction (maximum score 10) [88]. The IIEF has been reported to be a reliable and valid measure of erectile dysfunction [89] and is the most widely used measure within clinical settings to measure erectile dysfunction [90].

